#### Myocardial Structure and Function

Transthoracic echocardiography (TTE) will be performed to assess left atrial and left ventricular (LV) geometry and myocardial systolic and diastolic function. The Vivid *i *(GE healthcare, USA) with a phased-array ultrasound probe (S3) will be used for these measures. Patients will be positioned in the left lateral recumbent position.

LV dimensions will be obtained using two-dimensional (2D) and M-Mode measurements from the parasternal long axis window. Measurements of the interventricular septal wall thickness during diastole (IVSTd), posterior wall thickness (PWT), LV internal dimension during diastole (LVIDd) and LV internal dimension during systole (LVIDs) will be measured to derive the Left Ventricular Mass (LVmass).

LV mass will be calculated from LV linear dimensions using the ASE recommended formula:

LVmass = 1.04 ((LVIDd + PWT + IVSTd (3 - LVIDd)^3 ^× 0.8 + 0.6 g

These measures will then be divided by body surface area to obtain Left Ventricular Mass Index (LVMI).

Relative wall thickness (RWT) will be calculated using the American Society of Echocardiography (ASE) recommended formula [24]:

(2× PWTd)/LVIDd

Patients will have concentric hypertrophy if RWT > 0.42 with increased LV mass; eccentric hypertrophy if RWT < 0.42 with increased LV mass and concentric remodelling if the LV mass normal and RWT was increased[24]. Left atrial (LA) volume will be measured then indexed to BSA, using the area-length (L) method from the apical 4 (A4C) and apical 2 (A2C) chamber views in accordance with ASE guidelines [25]. L will be measured from the mid mitral annular plane and mid posterior LA wall, along its true long axis at end systole. During planimetry, the confluences of pulmonary veins and LA appendage are excluded.

LA Volume = (A_1_)(A_2_)/L × 0.85/BSA[26]

Where L = shorter length from either A4C or A2C. A_1 _= Maximal LA area from A4C. A_2 _= Maximal LA area from A2C.

LV systolic function will be assessed by calculating the ejection fraction (EF) using the disc summation method (Modified biplane Simpson's rule) [25]. Applying the following formula derives EF%:

$$\text{EF}\%=\frac{\text{LVEDV}-\text{LVESV}}{\text{LVEDV}}\times 100$$

Where LVEDV = left ventricular end diastolic volume, LVESV = left ventricular end systolic volume. For the purpose of this study, a normal EF will be ≥ 55% [25].

LV Diastolic Function will be performed using pulsed Doppler interrogations of the LV inflow tract from the A4C view. This will allow for the measurement of peak flow velocity of early (E) and late (A) LV filling. Early diastolic flow (deceleration time DT) and mitral A wave duration. The isovolumic relaxation time (IVRT) will be recorded from the A5C view using continuous wave Doppler interrogation.

Tissue Doppler Imaging (TDI) will measure the longitudinal velocities within the myocardium from the apical 4-chamber view, in pulse wave (PW) mode. This normally consists of a positive systolic wave (S') and 2 diastolic peaks, one during early diastole (E') and the second during atrial contraction (A'). The mitral E velocity and annular E' will be compared as a ratio (E/E'). An E/E' > 10 from the lateral wall is will be indicative of elevated LV filling pressures [26]. Recordings will be made from the lateral mitral annulus.

Pulse wave analysis (PWA) will be used to derive a central (ascending aortic) pressure waveform via applanation tonometry. This method involves using a generalised transfer function to generate a central pressure waveform, which we have shown to be valid [27]. Is a reproducible technique for measuring central blood pressure during hemodynamic perturbations induced by exercise [28]. The central waveform will be calibrated by the average of two measures of brachial blood pressure using a semi-automated device (UA-767, A&D). Central pulse pressure, central systolic blood pressure and augmented pressure will be recorded as markers of LV afterload.

#### Additional Measures of Arterial Stiffness

Augmentation index (AIx) is regarded as a measure of systemic arterial stiffness that will be derived from the central and radial pressure waveforms as previously described [29]. The ratio of brachial to central pulse pressure (pulse pressure amplification) will also be measured as a surrogate of large artery stiffness [30].

#### Oxidative Stress and Inflammation

Additional secondary outcome measures for oxidative stress and antioxidant status will include plasma protein carbonyls, total antioxidant capacity, plasma antioxidant enzyme activities, and for inflammation, C reactive protein and a cytokine panel consisting of IL-6, IL-8, IL-10 and TNF-alpha.

Additional data to be collected will include self-reported health (SF-36 questionnaire), physical activity levels (items from the Active Australia questionnaire) nutritional status (four-day diet diary), adverse events including mortality, morbidity, hospitalizations and procedures performed within the day procedure unit (e.g. iron infusions and arterio-venous fistula formation).

### Visit One (baseline data)

The study flow is summarized in Figure 1 and the study evaluations are outlined in Table 1. After obtaining informed consent, patients will be contacted by telephone by the trial coordinator at which a date and time is agreed for the subject to attend an appointment for baseline trial measures. A letter of confirmation of this appointment and a pathology request form will be posted (if consent formed is signed). Patients will be asked to attend the pathology laboratory at least seven days before their first trial visit to have a fasting blood sample collected. At the first trial visit, if not already done so, the consent form will be signed and additional data will be obtained from the medical records (medical history, medications) and measures of height, weight and blood pressure will be recorded. PWV, PWA, CIMT, TTE and BAR measures will then be made. At the completion of baseline data acquisition, the trial coordinator provides the subject with a pathology request form, for which blood samples are taken within the first week of visit one. The subject will be provided with two questionnaires (SF 36 and items from Active Australia) and a four-day diet diary for completion to take home. The subject is supplied with a self-addressed express post envelope. Subjects are asked to complete and post these within the following two weeks. Data obtained are transcribed onto case record forms for entry into a specifically designed trial database. Subjects are then reminded that they will be contacted by telephone in approximately five months to confirm an appointment date and time for visit two.

**Figure 1 F1:**
[figure not shown]
**Flow chart of the study**.

**Table 1 T1:** Outcome measures at baseline, 6 and 12 months

Primary Outcome Measures	
Arterial Stiffness	– Aortic Pulse Wave Velocity (PWV)
Oxidative Stress	– Plasma isoprostanes
Inflammation	– Plasma pentraxin 3
Secondary Outcome Measures	
Vascular Structure	– Carotid artery Intimal Medial Thickness (CIMT)
Vascular Function	– Brachial Artery Reactivity (BAR)
Myocardial Structure	- Left Ventricular Mass (LVmass)
	- Left Ventricular Mass Index (LVMI)
	- Left Atrial Volume
	- Left Ventricular Geometry
Myocardial Function	- Ejection Fraction (EF)
	- Early diastolic flow deceleration time (DT)
	- Isovolumic relaxation time (IVRT)
	- Ratio of mitral E and lateral E' (E/E')
	- Left ventricular afterload (central pulse pressure, central systolic pressure, augmented pressure)
Arterial Stiffness	- Augmentation Index (AIx)
	- Pulse pressure amplification
Oxidative Stress	– Plasma protein carbonyls
Antioxidant status	- Plasma total antioxidant capacity
	- Plasma antioxidant enzyme activities
Inflammation	– C reactive protein, IL-6, IL-8, IL-10 and TNF-alpha
Additional blood measures	- Full blood profile, electrolytes, liver function
	- Lipid profile
Self reported health	– SF 36
Physical Activity	– Items from the Active Australia questionnaire
Nutrition	– Four day diet diary
Adverse events	

### Visits Two and Three

These visits occur at six months and one year after commencement of dialysis. An envelope containing a letter confirming appointment, pathology request forms, four-day diet diary, SF 36 and physical activity surveys will be mailed to patients. They will be asked to complete surveys and the diet diary and to attend the pathology laboratory seven days prior to visits. At these visits, data acquisition from measures and tests described above will be performed again. Patients will be examined on a non-haemodialysis day for hemodialysis patients and during the non-dwell phase period for peritoneal dialysis patients.

### Withdrawal from Study

Subjects will be withdrawn from the study at their request, without prejudice, as documented and explained at the time of consenting.

#### Sample Size Estimates

Data from other studies indicates that pentraxin-3 has the highest variability of the three primary outcome measures (mean ± SD; isoprostanes = 54.1 ± 7.0 [46], PWV = 11.4 ± 2.4 [47], pentraxin 3 = 0.75 ± 0.3 [48]) and therefore will be used to estimate the sample size required. We assume that a decrease of 10% in pentraxin-3 would be clinically significant. Therefore, with alpha = 0.05 and beta = (1–0.8), we would need 23 patients in one of the groups. It is expected with an initial enrolment of 80 patients, 60 will complete the one-year measures. Based on the current distribution patterns within the renal services we estimate that 37 of these patients will be receiving haemodialysis and 23 receiving peritoneal dialysis.

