### Primary Objectives and Primary Outcome Measures

The primary objectives are to assess the effects of dialysis modality on arterial stiffness and oxidative stress and inflammation. The hypothesis is that peritoneal dialysis will significantly improve the rates of change in these measures compared with hemodialysis. The primary outcome measures are outlined below.

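### The 23 patients in one group do not follow from the stated pentraxin-3 inputs, which call for about 205 in the smaller group at the expected split

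*Protocol article*

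**What the plan says.** All of the following is in the Sample Size Estimates section of the protocol article unless another section is named.

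- The section states that "pentraxin-3 has the highest variability of the three primary outcome measures" and therefore bases the sample size on it. The value used is "pentraxin 3 = 0.75 ± 0.3". The other two primary outcomes are given as isoprostanes 54.1 ± 7.0 and aortic pulse wave velocity (PWV) 11.4 ± 2.4.
- Effect: "We assume that a decrease of 10% in pentraxin-3 would be clinically significant".
- Error rates: alpha 0.05 and 80% power. Sidedness is not stated.
- Conclusion: "we would need 23 patients in one of the groups".
- Expected numbers: "with an initial enrolment of 80 patients, 60 will complete the one-year measures", of whom "37 of these patients will be receiving haemodialysis and 23 receiving peritoneal dialysis".
- The Primary Objectives section gives the hypothesis that "peritoneal dialysis will significantly improve the rates of change in these measures compared with hemodialysis".
- The Statistical analysis section compares the mean per-patient rate of change between groups and corrects P-values for multiple comparisons by the Holm method.

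**The concern.** The section gives every input of a standard calculation and then a result those inputs do not produce. The gap is roughly ninefold in the smaller group (205/23 = 8.9). The inputs also describe a different quantity from the one analysed: 0.3 is presented as the SD of pentraxin-3 levels, while the hypothesis and analysis concern between-group differences in change over time. No SD of change and no within-patient correlation is given to connect the two.

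At stake is how the results are read. The Abstract says that the findings may guide the choice of dialysis modality in the first year. A reader told that the study has 80% power for a 10% difference in its most variable primary outcome could take a non-significant pentraxin-3 result as evidence that modality makes no difference.

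**Working it through.** **Inputs (Sample Size Estimates).** Mean 0.75, SD 0.3, difference 10% × 0.75 = 0.075, so d = 0.075/0.3 = 0.25. Alpha is 0.05 and power 80%. Completers are 23 and 37, ratio k = 37/23 = 1.609. Two-sided testing is my assumption; one-sided results are shown as well.

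**1. Trying to reproduce 23.** The normal approximation for the smaller group is n = (1.960 + 0.842)² × (1 + 1/k) / d², with (1.960 + 0.842)² = 7.849.

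- 1:1: 7.849 × 2 / 0.0625 = 251.2, so 252 per group (253 by noncentral t).
- 37:23: 7.849 × 1.622 / 0.0625 = 203.6, so 204 (205 by noncentral t, with 205 × 37/23 = 330 in the larger group).
- One-sided at 37:23: 161 in the smaller group.
- One-sample before/after test with SD 0.3: 7.849 / 0.0625 = 125.6, so 126 (128 by t). With 23 patients this test has about 21% power.
- Log scale at 37:23: 171 in the smaller group.
- Reading the 10% as an absolute 0.1 at 37:23: 115 in the smaller group.

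None of these gives 23.

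**2. Power at 37 v 23 if the SD of change is 0.3.** The standard error in SD units is √(1/23 + 1/37) = 0.2655. Then 0.25/0.2655 = 0.942, and power ≈ Φ(0.942 − 1.960) = 15.4% (15.3% by noncentral t). One-sided it is 24%.

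**3. Dependence on the missing SD of change.** With equal SDs at both times, SD of change = 0.3 × √(2(1 − ρ)). The correlation ρ is assumed throughout, because the article gives none. Noncentral t, 37 v 23, 10% difference in pentraxin-3:

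| ρ | SD of change | Power, two-sided 0.05 | Power, one-sided 0.05 | Detectable with 80% power, two-sided 0.05 |
|---|---|---|---|---|
| 0.5 | 0.300 | 15% | 24% | 30% of mean |
| 0.7 | 0.232 | 22% | 33% | 23% |
| 0.8 | 0.190 | 31% | 43% | 19% |
| 0.9 | 0.134 | 54% | 67% | 13.5% |
| 0.95 | 0.095 | 83% | 90% | 9.6% |

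**4. What would make 23 v 37 sufficient.** The detectable difference with 80% power at two-sided 0.05 is 0.7565 SD. The SD of change would have to be 0.075/0.7565 = 0.099, a third of the quoted SD. That implies ρ = 1 − (0.099/0.3)²/2 ≈ 0.945, between a pre-dialysis measurement and one taken a year after dialysis starts.

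**5. All three primary outcomes, taking each quoted SD as the SD of change (37 v 23, two-sided).**

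| Outcome | SD/mean | d for 10% | Power at 0.05 | Detectable, 0.05 (0.76 SD) | Power at 0.05/3 | Detectable, 0.05/3 (0.88 SD) |
|---|---|---|---|---|---|---|
| Pentraxin-3 | 40% | 0.25 | 15% | 30% | 7% | 35% |
| PWV | 21% | 0.475 | 42% | 16% | 26% | 19% |
| Isoprostanes | 13% | 0.773 | 82% | 10% | 67% | 11% |

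The 0.05/3 columns are the first Holm step with three primary outcomes.

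**The case against.** The strongest defence is that 0.3 is not the SD that matters. The analysis compares each patient's own rate of change, and a well-correlated marker can have an SD of change far below its SD of levels. At ρ = 0.95 the two-sided power is 83%. The directional hypothesis might also support a one-sided test. This much stands: a reader might infer that the planned analysis has only 15% power, and the article does not establish that. The 15% holds only for a two-sided test with an SD of change of 0.3. But the defence does not rescue 23, because the article states neither the smaller SD nor the correlation it requires.

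A reader might also infer that 23 was really calculated from the isoprostane values. By noncentral t, those inputs need 23 in the smaller group at 37:23 (22 by normal approximation), and isoprostanes are the least variable marker, not the most. But the match appears only when the 37:23 ratio is put into the calculation; at 1:1 they need 28 per group. The article introduces that split after the 23, as a forecast, and nowhere says isoprostanes were used. This is a possible explanation and no more.

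Finally, the study is observational with a convenience sample, it already plans 95% confidence intervals, and it presents itself as a possible step to a larger study. That limits the consequence to interpretation rather than conduct. It does not make the printed power claim correct.

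**Conclusion.** The point holds: on the stated pentraxin-3 inputs, 23 in one group is wrong. Those inputs need 253 per group at 1:1, or about 205 and 330 at the expected split, and the one-sided, one-sample, log-scale and absolute-difference readings all stay far above 23. This conclusion rests only on figures printed in the article.

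The actual power of the planned comparison is not known from the article. It is about 15% two-sided (24% one-sided) if the SD of change equals 0.3, and it reaches 80% two-sided only if that SD is about 0.10. The Holm correction makes the position less favourable for all three primary outcomes: at the first step, isoprostane power for a 10% difference falls from 82% to 67% on the quoted SD. These power figures take no account of the planned confounder adjustment.

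A reader might go further and want every non-significant primary result declared inconclusive in advance. That is not warranted, because a confidence interval could still exclude a 10% difference.

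**What to change.** Keep enrolment at 80 and rewrite the Sample Size Estimates paragraph as follows.

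- Delete the claim that 23 patients suffice for a 10% change in pentraxin-3, unless an SD of change near 0.10 can be given with its source.
- State the between-group difference in one-year change detectable with 80% power at 37 v 23. This is about 0.76 SD at unadjusted two-sided 0.05: about 30% of pentraxin-3, 16% of PWV and 10% of isoprostanes if the SD of change equals the quoted SDs. At the first Holm step (0.05/3) it is about 0.88 SD: about 35%, 19% and 11%.
- Say whether the test is one- or two-sided, and add a short table over assumed within-patient correlations, labelled as assumptions.
- State that a non-significant primary result will be interpreted by whether its 95% confidence interval excludes the 10% difference, and will not in itself be taken as evidence of no modality effect.

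The cost is one reworded paragraph and a less favourable stated figure. No extra patients, visits or analyses are needed.

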#### Statistical analysis

All baseline continuous variables between groups will be compared using general linear modelling, whilst categorical variables will be compared using exact logistic regression. The rates of change will be estimated for each patient separately by linear regression. general linear modeling, will be used to compare the mean rate of change in primary outcome measures between groups, unadjusted and adjusted for actual and potential confounding variables. Mean differences, 95% confidence intervals and P-values will be corrected for repeated measures, and P-values corrected for multiple comparisons by the Holm method. All analyses will be performed using Stata/IC 10.1 for Windows (StataCorp LP, College Station, Tx).

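### The 23 patients said to be needed for pentraxin-3 do not follow from the inputs printed beside that figure, which call for about 205 in the smaller group at the expected split

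*Protocol article*

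**What the plan says.** Sample Size Estimates names the outcome that drives the calculation, on the ground that "pentraxin-3 has the highest variability of the three primary outcome measures". It prints published values for all three primary outcomes, including "pentraxin 3 = 0.75 ± 0.3" and "isoprostanes = 54.1 ± 7.0"; aortic PWV is 11.4 with SD 2.4. The target is set for one outcome only: "We assume that a decrease of 10% in pentraxin-3 would be clinically significant". The error rates follow, "with alpha = 0.05 and beta = (1–0.8", and the conclusion is "we would need 23 patients in one of the groups". The section then expects 60 of 80 enrolled patients to complete and estimates that "37 of these patients will be receiving haemodialysis and 23 receiving peritoneal dialysis".

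It does not give sidedness, an SD of change or a within-patient correlation. Statistical analysis fits a regression slope to each patient, compares mean slopes between the dialysis groups, plans 95% confidence intervals and applies Holm correction to the P-values.

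**The concern.** The inputs and the result are printed together, and the result is presented as following from the inputs. A 10% decrease in an outcome with a 40% coefficient of variation is a small standardised difference, and 23 patients in one group is far too few for it under any usual formula.

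This is the only sample size justification in the article, and the reason for choosing pentraxin-3 implies that the less variable outcomes would then be covered too. If the figure is wrong, the study has much less ability to detect the pentraxin-3 difference it calls clinically significant than the stated 80%. A null pentraxin-3 finding could then be taken as evidence against a difference that the study was unlikely to see.

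**Working it through.** **Inputs (Sample Size Estimates).** Pentraxin-3 mean 0.75 and SD 0.3; 10% decrease; alpha 0.05; power 0.80; completers 23 v 37. Sidedness is not stated. Two-sided is the main case, because Statistical analysis plans 95% confidence intervals; one-sided is also tried.

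**Standardised difference.** 0.10 × 0.75 = 0.075, and 0.075 / 0.3 = 0.25.

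**Attempt to reproduce 23.** With (1.960 + 0.842)² = 7.849:

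- Two equal groups: 2 × 7.849 / 0.25² = 251.2, so 252 per group; the t-based solution is 252.1, so 253.
- Ratio 37:23 (1.609): (1 + 1/1.609) × 7.849 / 0.25² = 203.6, so 204 in the smaller group; t-based 204.4, so 205, against about 329 in the larger.
- One-sample or paired with SD 0.3: 7.849 / 0.25² = 125.6, so 126; t-based 127.5, so 128.
- One-sided, t-based: 199 per group at 1:1, 161 in the smaller group at 37:23, or 101 one-sample.
- Log scale, 37:23: 171 to 208 two-sided and 135 to 164 one-sided.

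None is close to 23. The smallest t-based figure, 101, is more than four times as large.

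**Power at 23 v 37 if the analysed SD is 0.3.** 0.25 / √(1/23 + 1/37) = 0.94, which gives 15% two-sided (15.4% normal, 15.3% t-based) and 24% one-sided. At 0.05/3, the first Holm step for three outcomes, it is about 7% two-sided.

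**Allowing for change scores.** The SD of a change is 0.3 × √(2(1 − ρ)), where ρ is the within-patient correlation. The document gives no ρ, so these values are assumptions:

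| Assumed ρ | SD of change | Power, 23 v 37 |
|---|---|---|
| 0 | 0.424 | 10% |
| 0.5 | 0.300 | 15% |
| 0.8 | 0.190 | 31% |
| 0.9 | 0.134 | 54% |
| 0.95 | 0.095 | 83% |

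Baseline-adjusted analysis over ρ from 0 to 0.9 gives 15% to 57%. For 80% power the SD of change must be about 0.099, so ρ = 1 − 0.099² / (2 × 0.3²) = 0.95. A one-sample calculation that returns 23 needs ρ of about 0.92.

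**What 23 v 37 can detect.** The t-based difference for 80% power at two-sided 0.05 is 0.757 SD. If the SD of the analysed quantity equals the published SD:

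- Pentraxin-3: 0.757 × 0.3 = 0.227, or 30% of 0.75.
- PWV: 0.757 × 2.4 = 1.82, or 16% of 11.4.
- Isoprostanes: 0.757 × 7.0 = 5.3, or 10% of 54.1.

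**Where 23 could come from.** At least two routes give it:

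- Isoprostanes with a 10% difference (5.41 / 7.0 = 0.773) at 37:23: t-based 22.07, so 23. The normal approximation gives 22, and equal groups need 27 to 28.
- Pentraxin-3 with the variance 0.3² = 0.09 used as the SD, equal groups, normal approximation: 2 × 7.849 × (0.09 / 0.075)² = 22.6, so 23.

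**The case against.** The strongest defence is that the planned analysis compares rates of change, while the printed SDs are not described as SDs of change. A much smaller SD of change could sit in the full protocol, which is not shown, so 15% cannot be called the power of the trial. That stands, and 15% is conditional here for that reason. It does not rescue 23, because the section draws 23 from the printed figures, and the correlation needed, about 0.95, is very high and nowhere stated.

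Two stronger readings are tempting, and the document supports neither:

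- A reader might infer that the sponsor sized on isoprostanes, the least variable outcome, by mistake. That match holds only at 37:23 with the t-based formula. The article gives 23 before it mentions the split and presents the split as an expectation from service patterns. The variance-for-SD slip gives 23 as well.
- A reader might infer that the study also fails a stated target for PWV. At 23 v 37, power for a 10% PWV difference would be about 42% on the published SD. However, the section calls a 10% change clinically significant for pentraxin-3 only and sets no target for PWV or isoprostanes.

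It is also fair to say that estimates with 95% confidence intervals are already planned, and that the Discussion presents the study as a possible step to a larger one. This limits the harm but does not correct the figure.

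**Conclusion.** The concern holds for pentraxin-3. The stated 23 does not follow from mean 0.75, SD 0.3, a 10% decrease, alpha 0.05 and 80% power; at the expected split those inputs need roughly nine times as many in the smaller group (205 / 23 = 8.9). This conclusion about the printed arithmetic needs no assumption beyond standard formulas, and it holds for one- or two-sided tests.

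The size of the power shortfall does rest on an assumption. It is about 15% power if the analysed SD is 0.3, and 10% to 54% for change scores if the within-patient correlation lies between 0 and 0.9, all at two-sided 0.05 before Holm correction. Sizing on the most variable outcome is therefore not achieved by the figure given. Which slip or unstated input produced 23 cannot be settled from the article.

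**What to change.** Keep 80 enrolled and 60 completers. In Sample Size Estimates, do one of two things:

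1. If an SD of change or a correlation was used, print it with its source and the sidedness, and show that it returns 23.
2. Otherwise, delete the claim that 23 patients suffice for a 10% decrease in pentraxin-3 with 80% power, and put in its place:

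> With 37 and 23 completers the study has 80% power (two-sided 0.05, before Holm correction) for a between-group difference of 0.76 SD of the analysed rate of change. If that SD equals the published single-time SD, this is about 30% of the mean for pentraxin-3, 16% for PWV and 10% for isoprostanes.

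In either case, add that a non-significant pentraxin-3 result will be reported as an estimate with its confidence interval and will not be read as excluding a 10% difference.

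The cost is one rewritten paragraph, with less favourable figures under the second option. No extra patients, visits or measurements are needed.
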